## Abstract

Depression is the most common psychological disorder during the perinatal period, and its negative effects extend to mothers, babies, their family and society. Scientific evidence points to the urgency of designing preventive interventions and concludes that the gestational period is the most appropriate time to implement these interventions. However, many pregnant women do not seek professional help due to a lack of knowledge about the importance of mental health, its impact, and the available intervention options, as well as a lack of time and financial resources. E-health interventions can be an efficient, cost-effective, and accessible resource for preventing postpartum depression that can circumvent the barriers that pregnant women face. This randomized clinical trial will examine the efficacy of Healthy Moms and Babies, an app aimed at preventing postpartum depressive symptomatology. The second objective of this study is to analyze the effectiveness of the tool in preventing anxious symptomatology. The primary outcome measure is the difference in the mean score between the intervention and control groups on the Patient Health Questionnaire-9 (PHQ-9) at the end of the intervention and at 3 and 6 months postpartum. The secondary outcome will be determined by using the Generalized Anxiety Disorder Screener (GAD-7) at the same time points. The research findings can be used to determine pregnant women’s use of the e-health application for the prevention of postpartum depression, whether the Healthy Moms and Babies intervention app is an effective and useful resource, and what modifications will need to be made to the tool in future updates.

## 1. Introduction

Depression is the most common psychological disorder during the perinatal period [1] and is a major public health problem that requires special attention [2,3]. Despite being a globally recognized and studied mental health condition, depression remains an underscreened and undertreated condition; much remains to be done for individuals with depression [4].

Perinatal depression is present worldwide. In the puerperal period, the prevalence of depression ranges from 4% to 63.9% depending on the country [5]. Rates of depression in industrialized countries range between 10% and 15%, but the rates are higher and increase to 20% in developing regions [6]. In Spain, the prevalence of moderate–severe depressive symptoms ranges between 14.8% [7] and 15.2% [8], and between 10.5% and 12.7%, during pregnancy and postpartum, respectively, depending on the time of assessment [9,10]. Furthermore, there is a high comorbidity between symptoms of perinatal depression and anxiety [11]. In Spain, the prevalence of anxiety ranges from 16.8% to 19.5% throughout pregnancy [12], and it is a strong predictor of postpartum depression [13].

The effects of perinatal depression extend beyond the mother, affecting the baby, partner, and family. Perinatal depression can disrupt caregiving activities [14] and the establishment of secure attachment [15]. Slomian et al. [16] categorized the negative outcomes of perinatal depression into three areas: (1) the mother’s physical and psychological health, with increased risk behaviors during the pre- and postnatal period (e.g., noncompliance with medical check-ups and unhealthy lifestyles); (2) the baby’s emotional, social, and behavioral development, with increased risk of lifelong psychopathology [17]; and (3) mother–baby interactions, including disruptions in breastfeeding and bonding.

Despite the negative consequences associated with perinatal depression, most women do not receive screening or treatment for perinatal depression although screening tools and evidence-based treatments are available [4]. Over 50% of women with antenatal or postpartum depression are unrecognized and undiagnosed, and few women (less than 20%) receive treatment [18]. Therefore, scientific institutions have stressed the need for interventions to prevent the consequences outlined above. In the United States (US), the Preventive Task Force [19] urges health professionals to refer women at risk for perinatal depression to counseling services. Developing successful psychological interventions to prevent perinatal depression improves parenting behaviors, it improves the quality of the mother–child relationship, and it enhances positive child outcomes such as better mother–child interactions or children’s mental health [20]. Moreover, the benefits of successful interventions appear to extend to the rest of society. The results of studies on the cost-effectiveness of preventive interventions for postpartum depression are still uncertain and inconclusive due to the methodological heterogeneity of the research [21], but the results are encouraging. The findings suggest that untreated perinatal depression may have important economic implications for the health care system. In the US, a mathematical model estimated that the societal cost of untreated perinatal mood and anxiety disorders from conception through 5 years postpartum was USD 14 billion for all births that occurred in 2017 [22], with more than half of the costs occurring during conception through birth. An Australian study suggests that if the prevalence rate of postpartum depression could be reduced by 5%, costs could be reduced by up to CAD 147 million [23].

As Muñoz et al. [3] point out, efforts should focus on preventing depression during pregnancy or the first weeks after childbirth for important reasons: (1) pregnancy and the twelve months after childbirth are a window of risk for the development of depressive symptomatology; (2) psychological interventions could be integrated in prenatal classes, which would reduce costs and associated stigma; and (3) the benefits of preventing depression extend to the baby even before birth. Pregnant women have frequent contacts with health services and are more willing to receive help because they believe it will have a positive impact on their baby [24]. However, there are barriers to seeking treatment and addressing prevention during this time. These barriers include the lack of information and knowledge about emotional problems and the available intervention options, as well as the practical limitations of access to treatment, such as the economic and time costs [25], which are closely related to putting the care of the child before the mother’s own care. Mental health illiteracy, myths and misconceptions promote prejudices about postpartum depression that are related to feelings of weakness and the belief of being a “bad mother”, which are other prominent barriers to seeking help [26]. Due to the stigmatization of mental health, especially in the perinatal period, women are reluctant to go to specialized units and prefer to receive care in obstetric and gynecological centers that are separated from mental health units [27]. Additionally, it is still difficult to find multidisciplinary teams in obstetric departments with a designated psychologist, and many women report the unwillingness of health professionals to attend to and support their emotional needs [28].

Given the advances in information and communication technologies, e-health interventions can help to overcome the aforementioned barriers, as these interventions preserve anonymity, are flexible and accessible [29], and can contribute to emotional and psychological literacy, making it easier for anyone to obtain information and help [3]. Systematic reviews on the effectiveness of e-health interventions for the prevention and reduction of depressive symptomatology in the perinatal period have concluded that such interventions can improve mothers’ moods [30] and reduce depressive symptoms [31].

Computer and internet-based e-health interventions have been developed and tested, but few studies have examined these interventions [29]. Danaher et al. [32] developed a web-based intervention program for postpartum depression called MomMoodBooster. The intervention program is comprised of six self-guided sessions, and it includes a weekly call from a therapist. It offers the ability to personalize the experience by uploading photos and setting goals and provides access to a private web forum for mothers to interact with their peers. The results indicated a statistically significant decrease in depressive symptomatology at the end of the program and at the six-month follow-up [32]. Fonseca and colleagues developed the Be a Mom program [33,34], which is a self-guided web-based intervention for postpartum women to prevent persistent postpartum depressive symptoms. The program is based on the principles of cognitive behavioral therapy and incorporates recent approaches based on third-generation therapies. The results suggested that the program promotes women’s self-compassion and improves their emotional regulation abilities, skills that exert a protective effect in the presence of risk factors for postpartum depression. Barrera et al. [35] adapted the Mothers and Babies Course to an online platform to prevent perinatal depression. Their results indicate that the benefits of participating in this online intervention were larger for pregnant women reporting high levels of prenatal depression symptoms. Furthermore, Duffecy et al. [36] developed a cognitive behavioral therapy internet intervention combined with peer support. The results suggested that women were responsive to both aspects to prevent perinatal depression. It is important to note that all the aforementioned interventions focused mostly on the psychological aspects (i.e., perinatal depression) without addressing other relevant content, such as breastfeeding, nutrition or the birth process.

In the field of e-health, mobile applications represent a tool with great potential in the gestational and postpartum periods. A study by Osma et al. [37] concluded that pregnant women use the internet more frequently from their smartphones than from their computers, with the mobile phone being the digital device that is most used by this population. Most women use pregnancy and parenting-related applications [38,39], and even women with few economic resources make use of these applications [40]. Pregnant women use applications for information when conventional antenatal care resources do not meet their needs or when they experience difficulty accessing these resources [41]. In addition, these applications allow for screening, assessment, and psychological interventions to be performed anywhere, anytime and at a low cost [42], increasing the chances of early detection and of providing rapid and appropriate interventions [43]. A meta-analysis of mobile application interventions for mental health confirmed their efficacy, highlighting their potential as cost-effective and accessible interventions for women who are unable to receive standard psychological treatment [44], and showed that these interventions offer promising results in improving and maintaining health. Notably, most of the research on perinatal depression prevention with e-health has been carried out in English-speaking countries [45] (e.g., the United States and Australia), while studies in Spanish are limited to Barrera and her colleagues. During 2019 [46], Spain reported 377,906 single births, 8134 double births, and 93 triple births or more; therefore, the number of women suffering from postpartum depression could range from 42,643 to 104,782. An application designed in the Spanish language will be very helpful to address the needs of the many women who could suffer depression all over the country.

The primary objective of the current study is to determine whether a Spanish preventive psychological intervention app designed in Spain, Healthy Moms and Babies, is superior to the general delivery of pregnancy information (breastfeeding advice, nutrition and exercise, birth facts, fetal development information and answers to frequently asked questions) in the prevention of postpartum depressive symptomatology. The secondary objective is to examine whether this same intervention is more effective than the general delivery of information about pregnancy in preventing postpartum anxious symptomatology.

## 2. Methods

### 2.1. Design and Population

The design is a two-armed randomized controlled study, with patients assigned to the intervention group, who will have access to the psychological content of the Healthy Moms and Babies app and general information about pregnancy, while those assigned to the control group, who will only have access to the informational content provided by the e-health tool. Participants will be assessed before and after using the app and at three and six months after their due date. Figure 1 shows a flow chart of the study design. Recruitment will take place between 2020 and 2022.

### 2.2. Recruitment of Women

#### 2.2.1. Identification and Recruitment in the Obstetrics and Gynecology Department

The obstetricians and midwives who collaborate in the research will invite pregnant women who are undergoing obstetric follow-up at the Hospital Clínico San Carlos in Madrid to participate in the study. Interested individuals will be given a leaflet explaining the research with a QR code that they can scan with their smartphone to visit the initial web form that collects contact and socio-demographic data (age, gestational week, place of origin and residence, reference hospital, completed studies, employment status, marital status, and number of pregnancies, cesarean sections and/or previous abortions).

#### 2.2.2. Mass Recruitment on Social Media

In parallel to recruitment at the hospital, announcements and ads will be published on the social networks, Twitter and LinkedIn, encouraging pregnant women from the general population to participate in the research study. Women will be provided with a direct link to the website of the Healthy Moms and Babies project (https://blogs.uned.es/mbc/, accessed on 26 November 2021), which, in turn, redirects them to the initial web form.

#### 2.2.3. Evaluation, Downloading Instructions and Accessing Passwords

Participants who complete the initial form will be asked to provide informed consent. Following this, women will receive a welcome letter and thank you email for their participation with instructions for downloading the Healthy Moms and Babies application and their personal access codes.

### 2.3. Outcomes and the Allocation of Participants to Trial Groups

#### 2.3.1. Primary Outcome

The primary outcome measure will be the difference in the mean scores between the intervention and control groups on the Patient Health Questionnaire-9 (PHQ-9) at the end of the psychological modules of the Healthy Moms and Babies application (in the case of the control group, the post assessment will be done six weeks after starting the PPP for the first time) and at three and six months after the delivery date.

The PHQ-9 is a nine-item instrument that assesses the severity of depressive symptomatology according to the following criteria of the Diagnostic and Statistical Manual of Mental Disorders [47]: depressed mood, markedly diminished interest in usual activities, significant increase or loss of appetite/weight, insomnia/hypersomnia, psychomotor agitation/retardation, fatigue or loss of energy, feelings of worthlessness or guilt, difficulty with thinking, concentrating or making decisions, and recurrent thoughts of death or suicide. The items are rated on four-point Likert-type scales, ranging from 0 (never) to 3 (almost every day), with higher scores indicating high severity of depressive symptoms (range 0–27). A score of 10 is the cut-off point recommended in clinical practice for estimating the presence of depressive symptoms [48,49]. However, considering that our aim is to prevent depressive symptoms, we will include all pregnant women who obtain a score equal to or greater than 5. The PHQ-9 has been validated in Spanish-speaking samples and in Spanish pregnant women [50].

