### 2.5. Randomization

When participants access the Healthy Moms and Babies application for the first time, they will complete the baseline assessment including the PHQ-9 and GAD-7. Only participants who score between 5 and 19 on the PHQ-9 will be included and randomized into the treatment and control groups.

Based on the PHQ-9 score, called the $value, the Plesk software will distribute participants according to their level of symptomatology. Participants scoring <5 on the PHQ-9 have minimal depressive symptoms and therefore they will be excluded from the study and no further evaluation will be performed, but they will be offered access to the pregnancy information content. Participants scoring >19 on the PHQ-9 are considered to have severe symptomatology and will also be excluded from the study. In this case, these participants will be blocked from accessing the Healthy Moms and Babies application because it was not designed to address severe depressive symptomatology. Women will receive an alert message telling them to share their distress with someone close to them and to see a specialist for appropriate psychological care. Eligible patients (PHQ-9 score between 5 and 19) will be randomly assigned to the intervention and control groups according to the standard PHP function (mt_rand()) automatically generated by a computer. Women in the intervention group will have access to the psychological content modules and the general pregnancy information on the Healthy Moms and Babies app; women in the control group will only be able to access the informational content.

An independent researcher will program the mathematical algorithm that performs the randomization. Subsequently, simple blinding will be used, and participants will not be informed of the group to which they are assigned. The allocation will be known to the study team after it is performed automatically.

Outcome measures will be assessed at baseline, immediately after the intervention, and three and six months after the delivery date. At follow-up, questionnaires will be sent at the appropriate time by email and will be completed by the women via a web form.

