### 3.3. Overview of the Intervention

The psychological intervention was comprised of eleven modules with a similar structure: an introductory video, psychoeducational content, a practical exercise, general guidelines, and motivational messages. Considering that a new module was released every 4 days, the average duration of the intervention was six weeks. The components of the intervention are described in the following paragraphs and Table 1.

*Module 1. You are a mum:* welcomes, collects and validates all the emotions and sensations that a pregnant woman may experience, inviting her to make use of the app to live consciously during her pregnancy. The practical activity allows the participant to reflect on her emotions related to her pregnancy.

*Module 2. Psychoeducation:* validates any emotions related to pregnancy and motherhood, reducing guilt, and encouraging responsible action. It provides some facts and information about the baby blues, perinatal depression, and its consequences. The practical activity consists of pointing out the depressive symptoms with which the woman identifies and naming the situations in which she does so.

*Module 3. Feel better:* presents the story of Violeta and María, two women who encounter the same day, but with very different experiences. It addresses the individual responsibility of making choices to increase the feeling of well-being. The practical activity invites the participant to create positive loops of activities, thoughts, and emotions to help her through difficult moments.

*Module 4.**Thoughts:* proposes that the participant listens to her thoughts and identifies the emotions she feels with each thought, inviting her to question them, release them or reformulate them when they generate discomfort and do not conform to reality. In the practical portion, the app challenges the woman to transform her most negative and harmful thoughts into healthier ones.

*Module 5.**Enjoy the day:* addresses the importance of planning and prioritizing pleasant activities each day, highlighting their potential benefits for emotional health. It proposes that the participant reflects on five pleasant activities that can be done in their daily life and offers guidelines for time management and how to practice these guidelines daily.

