### 3.4. Email Reminders to Increase App Utilization

When the app detects that the participant has not progressed in the modules for several days or weeks, it will send an email reminder to the mother to: (a) encourage continuing participation with the app, (b) inform the participant of subsequent topics; (c) offer the opportunity for the participant to ask questions or request support in the use of the tool; and (d) provide instructions to activate notifications as to when the next psychological module will be unlocked. If the participant continues to not use the application, up to three emails will be sent encouraging her to do so; following this, the participant is considered lost to follow-up.

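### The first post-baseline PHQ-9 is triggered by finishing the modules in the intervention arm but by a fixed six weeks in the control arm, so that one comparison is open to unequal timing and, by inference, to one-sided selection on completion

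*Protocol article*

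**What the plan says.** Section 2.3.1 sets three time points for the primary PHQ-9 comparison. For the intervention arm the first falls "at the end of the psychological modules of the Healthy Moms and Babies application". The exception for the other arm is in brackets: "in the case of the control group, the post assessment will be done six weeks after starting the PPP for the first time". PPP is not defined; I read it as the app. Section 2.3.2 takes the same time points for the GAD-7. Section 2.5 restates the schedule without a calendar anchor for the first point: "Outcome measures will be assessed at baseline, immediately after the intervention, and three and six months after the delivery date".

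Two later sections govern when an intervention woman reaches the end. Section 3.3 says "The psychological intervention was comprised of eleven modules with a similar structure" and adds "Considering that a new module was released every 4 days, the average duration of the intervention was six weeks". Section 3.4 provides for women who fall behind: "When the app detects that the participant has not progressed in the modules for several days or weeks, it will send an email reminder". A woman who still does not use the app gets up to three emails, and "following this, the participant is considered lost to follow-up".

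The article gives intervention women no latest date for the first assessment, and those who do not finish no alternative trigger.

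**The concern.** One arm is measured when the participant reaches an event that depends on her own pace after randomisation. The other is measured on a fixed day. Two problems can follow.

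- **Timing.** An intervention woman who runs late is measured further from baseline, and later in pregnancy or after birth, than a control woman randomised on the same day. Any change in PHQ-9 over those extra weeks that treatment did not cause enters the group difference.
- **Selection.** A woman who never finishes never reaches the event. If she is then not measured, the intervention mean describes completers and the control mean does not. Control women have no modules on which to stall, so the same filter cannot act on them.

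Both problems concern when, and from whom, data are collected. An analysis plan cannot recover scores that were never collected, and can realign scores taken at different times only under strong assumptions.

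**Working it through.** **1. The plan's own figure.** Inputs: 11 modules, 4 days between releases (section 3.3), control assessment at 6 × 7 = 42 days (section 2.3.1).

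- Module 1 on day 0: module 11 opens on day 10 × 4 = 40.
- Counting a full interval for every module: 11 × 4 = 44 days.

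Both are within 2 days of 42, so the stated six weeks is reproduced and the planned schedules match.

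**2. Average or minimum.** A woman cannot open module 11 before its release. Day 40 is therefore about the earliest finish, and departures run almost only later. Assumed paces show how the gap grows:

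| Days per module (assumed) | Reaches the end (10 or 11 intervals) | Days after the control assessment |
|---|---|---|
| 4 (release pace) | 40–44 | −2 to +2 |
| 5 | 50–55 | 8–13 |
| 7 | 70–77 | 28–35 |
| 10 | 100–110 | 58–68 |

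Section 2.4 allows entry at any point in pregnancy. Delivery can precede the first assessment in either arm; only the excess caused by delay differs between arms.

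**3. Who is measured.** Section 2.3.1 makes the end of the modules the trigger. Section 3.4 classes persistent non-users as lost. Section 2.5 gives controls only informational content. Read together, an intervention woman who stops has no route to a first assessment, whereas a control woman has a date.

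**4. Illustration of size.** The article gives no SD, drift, pace or completion rate. Assume SD 4.5 and the stated 385 women split evenly, about 192 per arm, all measured.

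SE = 4.5 × √(2/192) = 0.459

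Two-sided rejection at the 5% level when there is no true effect but a spurious difference b: 1 − Φ(1.96 − b/SE) + Φ(−1.96 − b/SE).

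- b = 0.2: b/SE = 0.435, rejection 7%.
- b = 0.6: b/SE = 1.306, rejection 26%.

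If only half of the intervention arm is measured (96 against 192), SE = 4.5 × √(1/96 + 1/192) = 0.5625, and the same differences give 6% and 19%.

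**5. Could selection alone give differences of that order?** Let c be the share who finish and r an assumed correlation between finishing and a lower PHQ-9. Then b = r × φ(t)/c × SD, where t is the normal quantile at 1 − c.

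- c = 0.7: t = −0.524, φ(t)/c = 0.348/0.7 = 0.497. With r = 0.1 to 0.3, b = 0.22 to 0.67. With 134 against 192 measured, SE = 0.507 and rejection is 7 to 26%.
- c = 0.9: b = 0.09 to 0.26, rejection 5 to 9%.

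So the range in step 4 is plausible at moderate completion and small at high completion. Every input in steps 4 and 5 other than the 385 women and the 5% level is assumed.

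**The case against.** The strongest reply is that six weeks was evidently chosen to match the programme, and on schedule it does, to within 2 days. Section 3.4 is a contingency and does not forecast how many women stall or for how long. Counting persistent non-users as lost also keeps many very late assessments out of the mean, so long delay and completer selection partly replace each other and should not simply be added. All of this stands. It limits the size of the bias but leaves the unequal trigger in place.

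The objective is postpartum symptoms, and the two assessments anchored on delivery address it most directly, with the same timing in both arms. This also stands, and it confines the point to one of three primary time points. The loss rule in section 3.4 could still thin the intervention arm at the later visits, but that is a separate matter.

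Three stronger readings are tempting, and the article does not support them:

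- **That it says non-finishers are not assessed.** No sentence says so. Section 2.1 speaks only of assessment before and after using the app, and the full protocol, not shown, may contain a fallback. The restriction to completers is an inference from the trigger and the loss rule.
- **That every control woman will be measured.** She has a scheduled date; whether she answers is unknown. Section 4 expects high drop-out in online interventions generally.
- **That the error rate is heavily inflated in a known direction.** Larger figures need an assumed weekly drift multiplied by an assumed mean delay. Regression to the mean after selection at PHQ-9 of 5 or more would be largely complete in both arms by six weeks, so it does not keep growing with delay. Symptoms could also rise late in pregnancy and reverse the sign.

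**Conclusion.** The point holds for the first post-baseline comparison of the PHQ-9 and the GAD-7, and only there. The unequal trigger is explicit in section 2.3.1 and nothing elsewhere reconciles it. The timing gap is about zero for women who keep to the release schedule, and grows almost only towards later assessment for those who do not. Selection on completion in one arm is a sound inference, not a stated rule.

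Neither size nor direction can be derived from the article. The rise from 5% to about 7 to 26% is an illustration that rests on an assumed SD of 4.5, about 192 women measured per arm and an assumed spurious difference of 0.2 to 0.6 points; it is lower if fewer intervention women are measured. The case for changing the rule rests on its asymmetry, which can be removed cheaply before data are collected and not fully repaired afterwards.

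**What to change.** In sections 2.3.1 and 2.5, set one rule for both arms: PHQ-9 and GAD-7 six weeks after randomisation (first access to the app), with the same window. Collect them whatever the module progress, through the emailed web form already planned for follow-up. Define the starting point in place of the unexplained abbreviation.

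In section 3.4, separate stopping use of the app from loss to follow-up, and keep sending the outcome form to women who stop. Report module completion as a measure of adherence, not as the trigger for the outcome.

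The planned difference in timing is then 0 days, and scheduling in neither arm depends on completion. The cost is a short text change and one email trigger. The downside is small: some intervention women will be measured before finishing all modules, which may slightly dilute the end-of-programme effect.
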